### **9.3 Stopping Rules**

There are no formal stopping rules for this clinical trial.

## **10 DATA COLLECTION AND HANDLING**

### **10.1 Data Management**

Source records are original documents, data, and records that are relevant to the clinical trial. The investigator will prepare and maintain adequate and accurate source documents, which are designed to record all observations and other pertinent data for each subject enrolled in this clinical trial. Source records will be adequate to reconstruct all data transcribed onto the CRFs (case report forms).

Participants will be given a unique random study number, and their data will be entered into this trial's database under their identification number.

After the study's database has been generated, the data will be submitted to the REC of Chinese PLA General Hospital for further review, when this trial is finished.

The clinical data, follow-up data, surgery video, and telesurgery system of the participants will be stored in the Telesurgery Research Center of Chinese PLA General Hospital. The written form will be stored in a locked filing cabinet, and electronic data will be stored in password-protected forms on the computers of the Telesurgery Research Center. The identification, screening, and enrollment logs will be stored at each trial site.

## **10.2 Data Collection, Handling, and Verification**

Authorized site personnel will enter all required data into CRFs. The investigator will be responsible for reviewing, verifying, and approving all subject data prior to the study's completion.

Source data in clinical trials includes paper and electronic forms. Paper source data is mainly recorded on paper carriers, which can be divided into the following categories: (1) data generated by the researcher or authorized personnel of the researcher for the first time, such as inpatient and outpatient medical records; (2) data generated by the subjects themselves, such as informed consent; (3) data generated by the validated electronic clinical outcome assessment system of the subject for the first time in paper form, such as test report forms of the inspection department; (4) other data recorded by the researchers or subjects, such as original notes, memos, and other paper documents generated for the first time during the clinical trial; (5) certified copies of the above source data, such as the original data signed and approved by the main researchers in the paper case report form. Electronic source data will be attached to the computer system in electronic form and will mainly include the following categories: (1) data generated by the researcher directly input on-site during the validation of electronic data collection; (2) data generated and stored in electronic form by the validated electronic system during the

formation of test reports, inspection reports, and other processes, and obtained through the validation of system transmission. All source data/files will be reasonably preserved in accordance with relevant laws, regulations, and SOPs. For example, paper source data files should be waterproof and fireproof, thermal paper data carriers should be timely archived, and electronic source data should be stored for a certain period of time. The investigator will have control over the source data generated in their testing facility. However, when using eCRFs, the investigator will directly control the input, modification, review, and signature of source data in the eCRF/electronic database through an authorized account. When using paper case report forms, the investigator will have full control over the source data in the paper case report form and will authorize the data entry personnel to modify the source data in the electronic database through the data clarification form. Permissions will be set up for control, access, verification, and review of data files, and appropriate work will be carried out only with the approval of permission to ensure the rights and interests of subjects and avoid unauthorized changes.

## **11 PEER AND REGULATORY REVIEW**

Obtaining funding of this trial from Chinese PLA General Hospital and National Natural Science Foundation of China and the process is

independent and sufficient rigour, which can be considered an adequate peer review.

## **12 ASSESSMENT AND MANAGEMENT OF RISK**

The risk posed to the control arm (i.e., the local surgery group) has been determined to be no higher than that of standard medical care. However, the trial arm (i.e., the telesurgery group) may have the potential risk of a malfunction of the telesurgery system with more complex structure and subsystem.

### **12.1 Emergency Plan for Telesurgery**

1) Network exceptions (including exceptions for image signals and control commands)

If the network is abnormal and cannot be recovered in time, the investigator will make a timely decision on whether to transfer to the local operation according to the on-site environment.

2) Abnormal operation during the procedure (such as the inability to effectively stop bleeding or perform an accurate operation)

If the network is normal but effective treatment is not possible at the patient end, the investigator will make a timely decision on whether to transfer to a local operation based on a quick discussion with the medical team.

### **12.2 Protection Strategy for the Telesurgery**

Firstly, the two surgeon consoles will be set up on both the planned first surgeon side and the patient side. The backup surgeon console will be used for the malfunction of the telesurgery system and can be used by the surgeon on the patient side to complete all the surgery steps.

Telesurgery has been adapted to the characteristics of remote operation. The real-time network latency is monitored by the system, and the surgery robot will be locked when the network latency is  $> 200$  ms.

## **13 RECORDING AND REPORTING OF EVENTS AND INCIDENTS**

### **13.1 Definitions of Adverse Events**

The Clavien-Dindo classification will be used to record the postoperative complications. All unexpected adverse events not included in this category will be recorded in the patients' medical notes. Any untoward medical occurrence in a patient will be defined as an adverse event, which may not have a causal relationship with the surgery.

A serious adverse event (SAE) is defined as any adverse event that results in death, is life-threatening, or results in any serious side injury to the participant during the surgery due to a malfunction of the telesurgery system.

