### **2.2.2 Perioperative morbidity**

To assess perioperative morbidity, the following clinical data will be collected:

1. Surgery-associated factors: intraoperative blood loss, operative time, and warm ischemia time (for partial nephrectomy).
2. Complications and adverse events: Adverse events will be recorded using the Clavien-Dindo classification at 4 weeks and 6 weeks postoperatively.
3. Postoperative hospitalization days.
4. Length of days in critical care.
5. Reoperational intervention.
6. Readmission to the hospital: Readmission to the hospital for any reason will be recorded, and the surgery-associated condition will be systemically reviewed.

7. Intra- and postoperative blood transfusion rates.

8. Mortality rate.

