### **5.2 Serious adverse events**

A serious adverse event is defined as any adverse event that results in death, is life-threatening, or results in any side injury to the participant during the surgery due to a malfunction of the telesurgery system.

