### **5.3 Malfunction of the surgery system**

The malfunction of the telesurgery system is defined as the system being out of control for any reason, such as a telecommunications pathway fault, a laboratory pathway fault, or a robotic fault. A malfunction of the local surgical robot is defined as the robot being out of control for any reason.

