### **8.4 Adverse event reporting**

Adverse events, adverse reactions, serious adverse events, and serious adverse reactions will be summarized.

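### The injury limb of the serious adverse event definition can be met only in the telesurgery arm, and its severity threshold differs between protocol 13.1 and SAP 5.2

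*Combined protocol and SAP*

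**What the plan says.** Protocol 13.1 defines an SAE by three limbs. Two are outcomes: "any adverse event that results in death, is life-threatening". The third is an injury limb, met when an event "results in any serious side injury to the participant during the surgery due to a malfunction of the telesurgery system". SAP 5.2 has the same structure, but its injury limb is met when an event "results in any side injury to the participant during the surgery due to a malfunction of the telesurgery system".

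Malfunction is defined separately for each arm. SAP 5.3 covers the telesurgery system and then adds: "A malfunction of the local surgical robot is defined as the robot being out of control for any reason". Protocol 2.2.5 does the same. The SAE definition uses only the first of these terms.

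SAE status has consequences. Protocol 13.2 requires entry in the CRF, a report to the chief investigator within 1 hour, and a meeting that reviews the surgery video and the monitoring data to find the cause. SAP 8.4 sets out the reporting: "Adverse events, adverse reactions, serious adverse events, and serious adverse reactions will be summarized".

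Other capture is not tied to an arm. Protocol 13.1 states: "Any untoward medical occurrence in a patient will be defined as an adverse event, which may not have a causal relationship with the surgery". It also states: "The Clavien-Dindo classification will be used to record the postoperative complications". Protocol 2.2.2 lists reoperation, critical-care days, transfusion and mortality, and adds: "Readmission to the hospital for any reason will be recorded". Protocol 3.6 collects obvious side injury straight after the operation.

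**The concern.** The trial's stated purpose is to compare the safety of telesurgery with that of local surgery. An SAE count serves that purpose only if the same event is classified in the same way in both arms. Here the injury limb requires a cause that cannot occur in the local arm. The same injury from the same kind of robotic fault would be an SAE in one arm and not in the other.

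There is also a problem of order. The meeting in protocol 13.2 exists to establish cause, but under the injury limb the cause must already be known before the event counts as an SAE. An injury of uncertain cause may never reach the review meant to explain it.

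The SAE route matters more because protocol 9.3 has no formal stopping rules and SAP 7 has no interim analysis. I found no other expedited safety review in the text.

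**Working it through.** **1. Design figure.** The plan gives no figure for SAEs, so there is none to reproduce. The sample size was checked only to see whether it depends on the definition. Inputs from protocol 9.2 are a success rate of 98% in both groups, a margin of 10 points, one-sided alpha 0.025 and power 80%. Then (1.95996 + 0.84162)² × (0.98 × 0.02 + 0.98 × 0.02) / 0.10² = 7.8489 × 0.0392 / 0.01 = 30.77, rounded up to 31 per group, as stated. No SAE term enters the formula, and the definition of surgical success (protocol 2.1, SAP 5.1) does not refer to SAEs.

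**2. The two definitions applied to the same events.** All events below are intraoperative injuries that are neither fatal nor life-threatening.

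| Event | Protocol 13.1 | SAP 5.2 |
|---|---|---|
| Serious injury, telesurgery arm, telesurgery-system malfunction | SAE | SAE |
| Lesser injury, telesurgery arm, telesurgery-system malfunction | not an SAE | SAE |
| Serious injury, telesurgery arm, no malfunction | not an SAE | not an SAE |
| Serious injury, local arm, local-robot malfunction | not an SAE | not an SAE |
| Serious injury, local arm, no malfunction | not an SAE | not an SAE |

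Rows 1 and 4 show the asymmetry between arms. Row 2 shows the difference between documents: if malfunction injures m telesurgery patients, m_s of them seriously, the protocol counts m_s and the SAP counts m. Row 3 is a case that the plan foresees. Protocol 12.1, item 2, describes difficulty in controlling bleeding or operating accurately while the network is normal.

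**3. Illustration of size.** The documents give no injury rates, so r and f are assumptions. Let r be the true rate of serious, non-life-threatening intraoperative injury, equal in both arms. Let f be the share of telesurgery-arm injuries caused by telesurgery-system malfunction. With the planned 34 per arm, expected injuries per arm are 34 × r. The injury limb counts 34 × r × f in the telesurgery arm and 0 in the local arm.

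| r | True injuries per arm | Chance of at least one in an arm, 1 − (1 − r)³⁴ | Telesurgery count, f = 0 | f = 0.25 | f = 0.5 | f = 1 | Local count |
|---|---|---|---|---|---|---|---|
| 3% | 1.02 | 0.645 | 0 | 0.26 | 0.51 | 1.02 | 0 |
| 6% | 2.04 | 0.878 | 0 | 0.51 | 1.02 | 2.04 | 0 |
| 10% | 3.40 | 0.972 | 0 | 0.85 | 1.70 | 3.40 | 0 |

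With equal true harm, this limb can add SAEs only to the telesurgery arm. With unequal harm it can also hide a difference. If r were 10% under telesurgery and 3% under local surgery, and no injury came from malfunction (f = 0), the true expected counts would be 3.40 and 1.02, but the limb would count 0 and 0.

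**The case against.** The strongest reply is that little is lost. Four parts of it stand.

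- A reader might infer that the whole SAE definition depends on malfunction. On the natural reading it does not: death and life-threatening events are separate limbs that apply in both arms whatever the cause. A life-threatening injury from the local robot is an SAE. The sentence could still say more clearly that the malfunction clause governs only the injury limb.
- A reader might infer that serious harms go unrecorded. They do not. Adverse events without a causality condition, graded complications, reoperation, readmission, mortality and side injury are collected in both arms. What is lost is SAE status and the review attached to it.
- SAP 8.4 only summarizes SAEs. No between-arm test of them is specified, and the comparisons of complications and adverse events under SAP 8.3.2 rest on arm-neutral definitions.
- Intraoperative injury can already count as a failure of the primary outcome. Protocol 3.6 excludes obvious side injury from completed surgery without any malfunction condition.

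It may also be said that SAP 5.2 governs the SAP 8.4 table while the protocol governs reporting, so the one-word difference is harmless. This stands only in part. The reach is narrow: it affects only non-serious injuries from telesurgery-system malfunction. But sites that follow the protocol would not record those events as SAEs in the CRF, so the SAP table could not count them reliably.

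None of this makes the injury limb reachable in the local arm or supplies a single severity threshold.

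**Conclusion.** The point holds in a limited form. As written, SAE counts, 1-hour reports and analysis meetings are not arm-neutral for serious intraoperative injuries that are not life-threatening, and the two documents set different thresholds for the same limb. The SAE summary should not be read as a like-for-like comparison of the arms. Recorded harms, the sample size and the primary endpoint are unaffected.

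The asymmetry follows from the wording alone. Its numerical size cannot be derived from the documents. Under the assumed equal rates of 3% to 10% with 34 per arm, it ranges from no difference to about 3.4 extra SAEs in the telesurgery arm, depending on the share due to malfunction. This assumes that patients receive the allocated type of surgery and that the malfunction clause governs only the third limb.

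Three stronger inferences are not supported. The documents give no rates from which to say that most serious surgical harms escape the SAE process. The distortion need not always run against telesurgery, because injuries without malfunction are left out in both arms. And the absence of limbs for hospitalization or disability cannot be called an error from these documents: nothing in them requires such limbs, and the regulations to which protocol 14.1 commits the trial are not reproduced.

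**What to change.** Reconcile protocol 13.1 and SAP 5.2 into one definition used in both documents:

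- Keep death and life-threatening events, stated to apply in both arms from any cause.
- Make the injury limb a serious intraoperative injury from any cause in either arm, with a single stated severity threshold.
- Record relation to telesurgery-system malfunction and relation to local-robot malfunction as two attribution fields, completed after review rather than required for entry.

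Optionally, the sponsor could consider whether reoperation and readmission, already collected in both arms, should also count as SAEs.

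The cost is an amendment to the wording of both documents, two attribution fields on the SAE form, and somewhat more SAE forms, 1-hour reports and meetings. Side injury and malfunction are already recorded, so no new clinical assessment is needed.

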### **13.2 Procedures for Recording and Reporting Serious Adverse Events**

All SAEs will be recorded in the medical records and the CRF.

SAEs will also be reported to the chief investigator within 1 hour. A SAE analysis meeting including the technique and surgeon group will review and analyze the SAEs as soon as possible. The video of the surgery and the telesurgery monitoring data will be reviewed to determine the cause of the SAE.

## **14 HUMAN SUBJECTS**

### **14.1 Ethical Considerations**

This clinical trial will fully be conducted in accordance with the ethical principles of the Helsinki Declaration, CFDA regulations, and REC requirements, adhering to the principle that the rights, safety, and will of the research subjects are paramount to the needs of research. Strict confidentiality measures will be taken for the research subjects, and their personal privacy will be respected to ensure that they will not suffer any discrimination or harm due to the results of the study.

### **14.2 Communication with the Research Ethics Committee**

This protocol, the ICF, the Investigator's Brochure, and any information to be given to the subject must be submitted to a properly constituted REC by the investigator for review and approval by the REC before the study is initiated. In addition, the REC must approve all subject recruitment materials before they are used for subject recruitment. The

investigator is also responsible for promptly informing the REC of any amendments or changes to the protocol or the Investigator's Brochure. Written documentation of REC approval must be received before the amendment is implemented.

### **14.3 Informed Consent Form**

No study procedure will be implemented prior to obtaining a signed, written ICF from the subject or the subject's legally authorized representative. REC review and approval are required for the ICF. If there are any changes to the ICF during the subjects' participation in the study, REC's written approval must be received, and subjects must consent to the revised version of the ICF before it is to be used.

Notes for the informed consent process are listed below:

(1) The researcher or the assigned responsible person will carry out the informed consent process.

(2) The informed consent process should cover every aspect related to the target subject's decision (whether to participate in the clinical study or not).

(3) Coercion, inducement, or imposition of inappropriate influence on the target subject should be avoided.

(4) The target subject will have the right to preserve their legal rights and interests.

(5) The target subject's native language will be used to provide intelligible and non-technical descriptions to facilitate their understanding.

(6) Sufficient time will be provided for the target subject to read and understand the "Informed Consent Form" and consider whether to participate in the clinical study.

(7) It should include the personal signatures of the target subject and the researcher or the assigned responsible person.

(8) The subject will be provided with a signed and dated copy of the "Informed Consent Form" or other handwritten materials.

(9) The procedure for obtaining and filling out the "Informed Consent Form" will be explained in special cases where the subject is unable to handle it themselves.

(10) Important new information will be provided to newly joined and current subjects throughout the entire clinical study process.

#### **14.4 Subject Confidentiality**

All data collected from this trial will be kept confidential to the extent required by law. Subject identification in clinical trial-related materials will primarily be based on random numbers and abbreviations of subject names in pinyin. Subjects' personal data will be recorded in a subject identification coding table, which will be kept confidential by the principal investigator. Personal information will not be disclosed without

the subject's written consent. The REC, CFDA, the Health and Health Commission Authorities of China, or the sponsor may access the personal data of subjects participating in the trial as needed, in accordance with established procedures. The content of this trial may be published, but any published content will not include any personal information about the subjects. Medical information on the subjects obtained as part of this study will be confidential and may only be disclosed to third parties as allowed by applicable regulations.

## **15 INDEMNITY ARRANGEMENTS**

The research group will hold insurance against claims from participants for harm caused by their participation in this clinical study. The hospital will continue to have a duty of care to the participants who have sustained injuries associated with this clinical trial.

## **16 PUBLICATION AND DISSEMINATION POLICY**

All materials and test results related to this clinical trial will be jointly owned by the researchers and the collaborators. The lead institution will have the right to publish a summary report of the clinical trial in the form of a paper, and the researchers from each participating institution will be entitled to authorship of the paper. However, consent from the collaborators must be obtained prior to publication. Before submission, any content intended for publication must be submitted to the

collaborators, who will review its accuracy, ensure that confidential information is not leaked, and supplement relevant information.

## 17 FUNDING AND SUPPLY OF EQUIPMENT

The study will be funded by the National Natural Science Foundation of China and the Foundation of Chinese PLA General Hospital.

The surgery robot system will be provided by EdgeMedical (Shenzhen, China). The telesurgery system will be built by the telesurgery research group of Chinese PLA General Hospital and EdgeMedical.

## **1. Introduction**

This SAP describes the statistical analyses to be performed for the data from the clinical trial entitled “A Prospective, Multicenter, Single blind, Randomized Controlled Trial on the safety and reliability of telesurgery robotic system on urology” (Protocol JF-MP-IITP-007). This clinical trial will be conducted to test the safety and reliability of telesurgery, which is a new developing field of surgery. This clinical trial will be led by Chinese PLA General Hospital.

## **2. Study Objects**

### **2.1 Primary object**

The primary objective of this clinical trial will be to evaluate and validate the safety and efficacy of telesurgery systems in urologic surgery compared with local surgery. The success rate of the surgery will be recorded.

